## Abstract

**Introduction:**

Adolescence is a challenging period for young people with type 1 diabetes, associated with worsening glycaemia and care disengagement. Educational interventions in this period tend to focus on diabetes-specific skills, with less emphasis on the psychosocial challenges associated with diabetes experienced by young people. To address this limitation, we codesigned with young people a psychosocially modelled programme of diabetes education, named ‘Youth Empowerment Skills’ (YES). The programme aims to facilitate a positive adaptation to life with diabetes and engagement with diabetes care through peer-based learning, immersive simulations and support from an outreach youth worker. Here, we present a protocol for a feasibility study of the YES programme.

**Methods and analysis:**

The study was designed following the Medical Research Council Complex Intervention Evaluation Framework to: test the feasibility (acceptance, implementability, recruitment and completion) of the YES programme; and estimate its efficacy in relation to metabolic and psychosocial outcomes. The study will take place in diabetes centres serving socioculturally diverse populations. We will conduct a feasibility randomised controlled trial (waiting-list design) with integrated process evaluation. Fifty young people with type 1 diabetes (aged 14–19 years) will be randomly allocated to either the YES intervention or a waiting-list control. Randomisation acceptability will be assessed with provision for a preference allocation. Outcomes will be evaluated at 6 months, at which point the waiting list participants will be exposed to the YES programme with further follow-up to 12 months. A simultaneous process evaluation will use a mixed-methods approach collecting qualitative and quantitative data. Study findings will be used to optimise the intervention components, outcome measures and recruitment methods to inform a subsequent definitive trial.

**Ethics and dissemination:**

The protocol has ethical approval from the UK Health Research Authority (approval IRAS project ID: 279877). Findings will be disseminated in multiple formats for lay and professional audiences.

**Protocol date and version:**

7 April 2021, V.1.1.

**Trial registration number:**

NCT04670198.

Strengths and limitations of this studyThe study will test a novel codesigned psychoeducational intervention for young people with type 1 diabetes designed to help promote a positive emotional and social adaptation to a life with diabetes.An integrated process evaluation within the study will develop our understanding of how to enhance study procedures and gain insights into programme implementation for future studies.The randomised waiting-list design allows for the comparison of the intervention and usual care exposures without the ethical implications of not providing the intervention to the control group.The target population for this study can be resistant to healthcare interventions and have significant school and social commitments; hence, the study will consider recruitment feasibility and the acceptability of randomisation versus preference for group allocation.

## Introduction

### Impact of type 1 diabetes on young people

Type 1 diabetes (T1DM) in adolescence and early adulthood can be a very challenging period in the lives of young people. During this period, young people can begin to dissociate from their diabetes, leading to a decline in their glycaemic control and an increased risk of acute events such as recurrent diabetic-keto-acidosis (DKA).^1–5^ Data from the most recent National Paediatric Diabetes audit in the UK showed that only 10% of young people aged 14–19 years achieved a glycated haemoglobin (HbA1c) within the current target range of ≤48 mmol/mol (6.5%); and a fifth had an HbA1c>75 mmol/mol (9%) which is associated with a high risk of diabetes complications.^3^

Furthermore, adolescence and early adulthood are also a period when young people are forming their personal and social identities, and diabetes can have a detrimental impact on their psychosocial development.^6 7^ During this period, young people can develop negative emotional constructs about diabetes, as they see their diabetes as an impediment to social relationships and life opportunities.^8^ Consequently, some young people may develop maladaptive coping strategies such as avoidance (omitting insulin and reducing their glucose monitoring), or psychological morbidities (fear, anxiety, depression and disordered eating behaviours).^9–11^ Young people with diabetes can also feel stigmatised,^12^ further driving negative coping strategies (eg, not using insulin in public or running glucose levels high to avoid hypoglycaemia).

During this period, young people are also developing their personal autonomy, which can lead to conflicts with parents who may find allowing the young person to take control over their diabetes self-management behaviours and health management challenging.^13^ Relationships can become emotionally charged with conflict, excess vigilance and distress, difficulties that can exacerbate disengagement and are associated with poorer glycaemic control.^14 15^ Negative interactions with diabetes health professionals have also been identified as contributing to young people disengaging from their care.^16^

### Current care models for young people with T1DM

Developing effective diabetes care for young people with T1DM is challenging. The transition from child to adult care has long been identified as a period when young people can disengage from their care, despite much innovation.^17–22^ In part, this is attributable to the failure of current care provision to adequately integrate the needs or life contexts of young people within that care. Young people with T1DM need support to help them develop the psychosocial skills necessary to transition positively into an adult life with diabetes, and to enable them to engage productively with healthcare providers. However, the main focus in diabetes guidelines is on intensifying glucose levels with diabetes technologies and structured education.^23 24^ Therefore, most current education programmes for young people aim to enhance self-management skills such as carbohydrate counting and insulin-dose adjustment, to help optimise glucose levels; rather than addressing how to integrate living with diabetes in relation to the wider interpersonal and social challenges that they experience in this period. Hence, while these programmes are generally effective in the adult diabetes population, young people are less likely to participate in these programmes. A recent study of 227 young people identified that the main reasons for their non-participation were a lack of time and a preference for managing their diabetes on their own.^25^ This indicates the need to reconsider both the type of educational support provided and how it is delivered to young people. While some programmes have been adapted for younger people, there is still an emphasis on technical aspects of diabetes,^26^ rather than psychosocial adjustment.

Therefore, new educational programmes are required for young people, to ensure that what they learn about managing their diabetes is contextualised with learning to live with diabetes in relation to their social and emotional development. It is also important to explore innovative methods of delivering education to young people with T1DM to make programmes more relevant, attractive and accessible to them.

### The Youth Empowerment Skills programme for young people with T1DM

The Youth Empowerment Skills (YES) programme is a novel psychoeducational intervention, which was developed through a codesign process with young people with the fundamental goal to overcome some of the challenges reviewed above. The codesign process sort to build the programme so that it addressed many of the previously identified challenges experienced by young people with diabetes. The programme uses three well-established psychological theories: social learning theory,^27^ self-regulatory theory^28^ (personal identity) and dual-process theory.^29^ These theories have been integrated into a learning model addressing: cognitive factors (knowledge, experiences, thinking processes and attitudes); environmental factors (exploring social norms and external factors that mediate behaviour); and behavioural factors (developing skills and self-efficiency, with practice, observation and rehearsal). This underpinning theory is delivered using different learning techniques: experiential and group-based learning; immersive simulations with scenarios such as treating an episode of severe hypoglycaemia or ketosis; and learning together in adventurous activities. The programme curriculum comprises the following sessions:

Diabetes as a part of daily life.The psychological impact of diabetes.Staying safe while being away from home (parties/alcohol/drugs and diabetes).Immersive simulations (hypoglycaemia, DKA, impaired physical function).Reverse role-playing of health consultations (how to get more out of a consultation).Relationships (peers/partners/family).Attitudes towards food, weight and eating out.Getting to know your body (foot-care/eye screening/sexual health).Exercise and diabetes (activity-based sessions, eg, rock climbing).How to prevent diabetes emergencies.

The programme is delivered by a peer educator with T1DM, health professionals and youth workers. The youth workers also do outreach work to identify potential participants and encourage them to attend. The programme is fully manualised and Quality Institute for Self-Management Education accredited.

As part of the programme’s development, we undertook a systematic review to identify studies of psychosocially modelled educational interventions and youth worker deployment in young people with T1DM. We found a limited number of studies that incorporated some elements of the YES programme but none that shared the same theoretical approach with strategies explicitly focused on the same target behaviours.^30–33^ Hence, the YES programme is a distinct, codesigned and theoretically modelled intervention, with novel components. A pilot evaluation of three early implementations of the YES programme that included 26 participants (mean age 18±1.7 years) showed it to be impactful on glycaemic control, with 46% (n=12) of participants achieving a clinically significant reduction in their HbA1c (≥5.5 mmol/mol or 0.5% DCCT/Diabetes Control and Complications Trial units) at the 12-month follow-up. Programme uptake was 34% (n=26) with 96% (n=25) programme completion, which is similar to other programmes targeting young people.^25^ Qualitative findings suggested that the programme had a positive psychosocial impact resulting in increased diabetes engagement and activation. The following active ingredients of the programme were also identified: social learning, peer support, relational care/support and experiential learning. The youth worker was also highlighted by participants as being important in engaging them with the programme.

In the study outlined in this protocol, we propose to undertake a feasibility trial of the YES programme, with an integrated process evaluation. We have modelled the active ingredients of the programme to target outcomes related to psychosocial well-being, diabetes self-management activation and glycaemic control. In the process evaluation, we will examine methodological, procedural and clinical uncertainties around the YES programme,^30–32^ including: (1) estimates of likely recruitment and retention rates; (2) feasibility and acceptability of data collection instruments and data collection procedures; and (3) feasibility and acceptability of the programme. In line with standard feasibility study objectives,^31^ we will not be testing the effect of the programme on outcomes, although we will estimate the impact of the programme on outcomes, to: consider the feasibility of progression to a definitive trial; and to inform a sample size calculation for such a trial. There will also be a mixed method element to the process evaluation,^32^ to explore: (1) intervention acceptability; (2) the intervention experience and its impact on physical, mental and social well-being; and (3) parents’ perspectives on the programme. These findings will be integrated to formulate potential mechanisms of change following programme exposure.

### Aims and objectives

The aims of study are to: test the feasibility of the YES programme in terms of programme acceptance, implementability, recruitment and completion; and to estimate its efficacy in relation to clinical, psychosocial and healthcare outcomes. The study objectives are to:

Evaluate and optimise the research process: recruitment, willingness to be randomised, consent procedures and data collection.Evaluate our ability to assess the programme’s impact on self-management, patient activation and clinical and psychosocial outcomes (optimising outcome selection and estimating the level effect).Establish the reach, fidelity, utility, feasibility, appropriateness, unintended consequences and sustainability of the YES intervention.Identify and explore the experiences of programme participants and those delivering the intervention.Optimise the intervention components, procedures and outcome measures.Obtain estimates of outcomes to inform the sample size calculation for a larger clinical evaluation study.

## Methods and analysis

### Study design

The study has been designed as a feasibility waiting-list randomised controlled trial (RCT) with an integrated process evaluation. Participants will be randomised to YES exposure (phase 1) or a waiting list control and followed up for 6 months. At the 6-month follow-up point, control participants will then be exposed to YES, in a phase 2 exposure. Both groups will be subsequently followed up for a further 6 months. This will ensure that all eligible young people will have the opportunity to participate in the programme while maintaining a controlled structure to YES exposure that will allow us to explore differences. Conducting an additional 6-month follow-up after phase 1 will also enable us to assess how sustainable the intervention is over a longer time period. The adoption of a waiting list design is important as it overcomes the ethical dilemma of denying control participants the opportunity to benefit from the programme. The study design is presented schematically in figure 1.

**Figure 1 F1:**
[figure not shown]
Consort diagram for the Youth Empowerment Skills programme feasibility study.

We have set the following progression criteria for a subsequent definitive trial: achieve minimum 30% recruitment of eligible participants; and ≥80% completion of final follow-up. We will also assess the impact of the intervention ingredients on target behaviours, including activation of self-management, engagement in diabetes healthcare and improved psychosocial functioning. These effects, alongside impact on glycaemic control, will be used to consider whether there is adequate potency in the programme and will determine whether a definitive trial will be conducted.

### Setting

The study will be conducted in South London, UK, recruiting participants from the diabetes centres of five hospitals, providing care to the target population. These sites have been selected to ensure sociodemographic diversity, with a significant proportion of patients from lower socioeconomic backgrounds and from Black Asian and Minority Ethnic populations. The study is planned to start on 1 June 2021, and finish 31 March 2023.

### Participants and sample size

We aim to recruit 50 young people and randomise half to the phase 1 programme exposure, and half to the phase 2 exposure. The inclusion criteria will involve:

Age 14–19 years.Diagnosis of T1DM.Suboptimal glycaemic control (HbA1c>69 mmol/mol or 8.5%).^3^No current or planned attendance of other structured education programmes.

Participants will be excluded if they: have a severe physical or mental illness, unstable retinopathy, significant learning difficulties; are unable to communicate in English; or are pregnant. Participants meeting the inclusion criteria will be recruited opportunistically at the participating centres through clinical referrals and patient database searches. Based on recruitment to the pilot study, we estimate that we will be able to recruit >30% of eligible patients. To increase engagement, we will run the full study, including programme occurrences and follow-up sessions, during school holidays as this was identified by young people as the optimal period for running the YES programme.

As a feasibility evaluation, the study is not statistically powered to estimate a clinical effect. Instead, we aim to estimate the effect-size/SD of outcomes to formulate a power calculation for a definitive trial. National Institute for Health Research guidance indicates that samples of 24–50 are adequate for this purpose.^33–35^ We have inflated our sample to allow for an estimated 20% drop-out rate.

### Intervention and control conditions

The intervention is the YES programme as previously described. The programme exposure is sequenced as follows: (1) initial contact from the youth worker introducing the YES intervention; (2) recruitment to the study by researchers; (3) attendance at three all-day YES sessions in non-healthcare settings (groups of 10); (4) postprogramme networking through social media and (5) follow-up events facilitated by the youth worker. Sessions will be led by a peer-educator and a health professional and delivered face to face. Participants in the waiting-list control arm of the study will receive usual care following initial randomisation and will be exposed to the YES intervention at 6 months (phase 2 exposure). Usual care in this patient population typically involves outpatient consultations. To minimise potential external confounding factors, we will monitor any other educational interactions that participants might experience during the follow-up period in both groups.

### Randomisation

Participants will be randomised to either the phase 1 YES exposure or to the waiting list control (for phase 2 exposure), using computer-generated randomisation in blocks of 20. This will be conducted by a member of the study team not involved in recruitment. As the intervention is open, blinding is not possible. The waiting list design will help to maintain young people’s motivation to participate in the phase 1 and 2 allocations. As part of our feasibility work, we will consider how acceptable randomisation is to young people with diabetes. Young people’s lives are quite dynamic in this period with frequent changes such as moving schools starting further or higher education, or employment. Hence, while we will explain why randomisation is helpful to us, but if young people decline randomisation they will be offered a preference for when they join the programme.

### Outcome measures

As a feasibility study, the objective is to optimise outcome selection and determine outcome effects prior to a definitive RCT. The primary outcome to assess the potential clinical effect of the programme will be HbA1c and we will examine: (1) the number of participants achieving clinically significant reductions of 5.5 mmol/mol or more and mean differences between groups over time, and (2) the SD of the mean difference between the intervention and control group in HbA1c at 6 months; for the control group, the SD of the mean difference between HbA1c at 12 months and preexposure (phase 2) and for the phase 1 intervention group, the SD of the mean HbA1c difference between post (6 and 12 months) and pre-exposure. While HbA1c is a proxy measure of complication risk, it is the most commonly adopted measure for determining the short to medium-term impact of an intervention and is the recommended measure from the National Institute for Health and Care Excellence for assessing the clinical and health economic benefits of diabetes interventions. In addition, our preliminary work and logic model show that the programme can mediate health behaviours by impacting on the psychosocial factors that can mediate self-management activation leading to improved glucose control. Hence, we will also assess the psychosocial and behavioural impacts of the programme, using the following secondary outcome measures:

Number of participants with 20% increase in frequency of blood glucose monitoring.Insulin adherence measured by self-report scale.Self-Management of Diabetes in Adolescence Scale.^36^Confidence in managing own healthcare (Confidence in Diabetes Self-Care Scale.^37^Diabetes Quality of Life Instrument-adapted for youth.^38^Illness perception (Brief Illness Perception Questionnaire).^39^Emergency care events (ambulance call-outs, accident and emergency attendance or hospitalisations).Hypoglycaemia (blood glucose<3.5 mmol/L) and severe hypoglycaemic events (requiring third party assistance).Weight.Intervention Appropriateness Measure.Feasibility of Intervention Measure.Acceptability of Intervention Measure.

For each outcome, we will assess differences in preexposure and postexposure, as well as differences between control and intervention groups.

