### Data analysis

The data will be analysed to determine the proportion of patients achieving the progression criteria; and the target reduction in HbA1c from baseline to follow-up (6 and 12 months), which will be estimated in both intervention (YES) and control groups. We will also estimate the SD of the mean difference between the intervention and control group in HbA1c at 6 months; for the control group, the SD of the mean difference between HbA1c at 12 months and pre-exposure (phase 2) and for the phase 1 intervention group, the SD of the mean HbA1c difference between post (6 and 12 months) and pre-exposure. These data will help inform the sample size calculation for a definitive trial.

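### Glucose monitoring is defined only as a count of participants with a 20% relative increase; frequency should also be reported as a continuous outcome with its SD

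*Protocol article*

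**What the plan says.** In the Protocol article, Outcome measures, the first secondary outcome is "Number of participants with 20% increase in frequency of blood glucose monitoring". No mean, absolute change or SD of testing frequency is named beside it.

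The same section treats the primary clinical outcome, HbA1c, differently. It will examine "the number of participants achieving clinically significant reductions of 5.5 mmol/mol or more and mean differences between groups over time", and it goes on to list SDs. The section closes with a general statement: "For each outcome, we will assess differences in preexposure and postexposure, as well as differences between control and intervention groups".

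Under Participants and sample size the purpose is put in the plural: "we aim to estimate the effect-size/SD of outcomes to formulate a power calculation for a definitive trial". Under Data analysis the only SDs named are for HbA1c ("We will also estimate the SD of the mean difference between the intervention and control group in HbA1c at 6 months", followed by two within-group SDs), and the text then adds "These data will help inform the sample size calculation for a definitive trial".

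Data collection and storage names blood glucose testing among the self-management behaviours recorded at baseline. The matching follow-up item is not named, but the 20% rule cannot be applied without it.

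**The concern.** The article uses the sound approach for HbA1c, a responder count alongside the continuous summary, but not for monitoring. Four things follow from using the count alone.

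- **Lost information.** A rise from 1 to 1.2 tests a day scores the same as a rise from 5 to 6, and everything short of the threshold scores as nothing.
- **No value at zero.** A 20% increase on a baseline of zero is undefined.
- **No SD of frequency.** The study cannot then show whether testing frequency would be a usable outcome in the definitive trial. Optimising outcome selection is one of its stated objectives.
- **Poor fit with the pre/post analysis.** A count of people who increased is already a change and has no pre-exposure value. Chance crossings have nothing to be compared with there and can be read as response.

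The Study design section says that effects on self-management activation will help decide whether a definitive trial goes ahead. Testing frequency is a direct behavioural measure of that activation.

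**Working it through.** **The plan's own figure.** The only design figure is a total of 50, inflated for 20% drop-out. The base is not stated. Solving back, 40/(1 − 0.20) = 50, and 40 lies inside the cited range of 24 to 50. The monitoring outcome plays no part in this.

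**Cost of the cut-off.** For a normal outcome cut so that a proportion p respond, with φ the normal density at the cut-point t, relative efficiency = φ(t)²/[p(1 − p)].

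- p = 0.2: 0.49
- p = 0.3: 0.58
- p = 0.4: 0.62
- p = 0.5: 0.64

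As an illustration, take a future trial with two-sided α of 0.05 and 80% power. The standardised differences are assumed, as the article gives none.

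| Standardised difference | Continuous, per arm | Responder count, per arm (control responders 40% to 20%) |
|---|---|---|
| 0.5 | 63 | 100 to 115 |
| 0.3 | 175 | 276 to 329 |

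**Crossing by chance.** The article gives no testing rate, counting window or within-person variance, so all three are assumed. Two independent counts with the same mean (tests per day × days) were simulated in 400,000 pairs. The entry is the percentage with second count ≥ 1.2 × first, among pairs with a non-zero first count.

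| Window, variance | 1/day | 2/day | 4/day | 6/day |
|---|---|---|---|---|
| 7 days, Poisson | 37.9 | 32.3 | 25.4 | 20.6 |
| 14 days, Poisson | 32.3 | 25.4 | 17.2 | 12.2 |
| 28 days, Poisson | 25.4 | 17.1 | 8.8 | 4.8 |
| 7 days, variance 2 × mean | 41.4 | 37.6 | 32.0 | 28.1 |
| 14 days, variance 2 × mean | 37.4 | 32.0 | 25.1 | 20.5 |
| 28 days, variance 2 × mean | 31.9 | 25.1 | 16.9 | 12.0 |

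The range is about 5% to 41%. A lognormal model with within-person CVs of 10%, 20%, 30% and 50% gives 10%, 26%, 33% and 39%.

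A one-day window behaves differently. At 1 test a day (Poisson) 36.8% have a zero baseline and 17.8% of the rest cross, against 40.8% at 4 a day.

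If frequency is recorded in whole tests per day, one extra test meets the rule for any baseline of 1 to 5, and two are needed for 6 to 10.

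**Effect on the comparison.** Suppose a fraction π of the intervention arm truly respond and all of them cross, no control participant truly responds, and everyone else crosses with probability c. The expected difference in proportions is [π + (1 − π)c] − c = π(1 − c). At c = 0.05 this is 0.95π; at c = 0.41 it is 0.59π. With π = 0 the difference is zero, so the comparison is diluted but not biased away from no effect. In a single-group pre/post reading, c itself appears as response.

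**Precision here.** For proportions near 50%, the 95% half-width of the difference is 1.96 × √(2 × 0.25/n): about 28 percentage points with 25 per arm and 31 with 20 per arm.

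**The case against.** A reader might infer that the power calculation for the definitive trial is left without an SD. The article does not support that. The planned SDs are for HbA1c, the primary clinical outcome, and Data analysis ties the sample size calculation to them. Nowhere is monitoring frequency proposed as the outcome on which to size that trial, and a responder proportion has its own binomial variance and could size a binary outcome.

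A reader might also infer that the SD of frequency is lost. It is unplanned in this text, but not out of reach: frequency at both times is needed to apply the 20% rule.

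A third tempting reading is that the trial population are low testers, so that the count would be mostly noise. The Introduction says only that some young people may cope by testing less. Eligibility rests on HbA1c and has no testing criterion, and no testing rate is given. High testers cross by chance too, and in one-day counts the gradient by testing rate reverses.

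It is also fair that a condensed article may leave the counting window, data source and zero-baseline rule to the full protocol or SAP. Their absence is not the complaint. Finally, the study does not set out to test effects, and other listed measures, such as the self-management and confidence scales, bear on the same construct.

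What stands after all this is the stated choice itself: monitoring is a relative cut-off count and nothing more, next to an HbA1c outcome kept both ways and an aim to estimate effect sizes and SDs of outcomes in the plural.

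**Conclusion.** The point holds as a minor one. Using the count alone costs roughly 36% to 51% of the information (1 − 0.64 to 1 − 0.49), assuming a normal outcome and response rates of 20% to 50%. It leaves a zero baseline without a value and yields no SD of monitoring frequency.

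Chance crossing of about 5% to 41% rests wholly on the assumed testing rates of 1 to 6 a day, the 7- to 28-day windows, and Poisson or twice-Poisson variance. It shows that the threshold can be crossed without change; it is not a forecast for this trial. The consequence is dilution between randomised arms and possible misreading of the uncontrolled pre/post change. It is not a biased randomised comparison.

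The HbA1c SDs, the sample of 50 and the two numeric progression criteria (at least 30% recruitment, at least 80% completion) do not change.

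**What to change.** Add to the outcome wording: blood glucose monitoring frequency at 6 months as a continuous outcome, compared between randomised arms with adjustment for baseline frequency, and reported with its SD. Keep the number with a 20% increase as a descriptive extra, and state that it is not computed for participants with a zero baseline.

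The cost is slight: a little more analysis, and making sure the raw frequency, not just the yes/no classification, is retained at follow-up in the same form as at baseline. No extra participants or visits are needed.

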### Data collection and storage

Data (questionnaires, body weight and medical-record data) will be collected at baseline, then again at 6 and 12 months. Baseline data will also include: sociodemographics; education/employment; and diabetes self-management behaviours including insulin use and blood glucose testing. Patient records will be examined to collect data on: HbA1c; hospitalisations and emergency care; diabetes education attendance; screening attendance; and attendance at appointments. For baseline, this will be all events in the preceding 12 months, and postexposure will be for the 12 months following exposure (or 6 months’ post exposure for those exposed at phase 2). Analysis will be on-treatment, as the primary aim of this study is to assess feasibility. Data will be coded and cleaned by statisticians and stored on an encrypted shared drive.

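### Within-group change in body weight is confounded with growth in participants aged 14–19, and no height is listed from which a growth-standardised measure could be derived

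*Protocol article*

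**What the plan says.** Weight is one of the 12 secondary outcomes under Outcome measures, with no unit, scaling or derivation. The sentence that closes that section applies two contrasts to every outcome: "For each outcome, we will assess differences in preexposure and postexposure, as well as differences between control and intervention groups".

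On measurement, the section Data collection and storage says: "Data (questionnaires, body weight and medical-record data) will be collected at baseline, then again at 6 and 12 months". It then lists further baseline items and the items taken from patient records. Height and BMI appear in neither list.

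The first inclusion criterion is "Age 14–19 years".

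On the comparator, Study design says: "Participants will be randomised to YES exposure (phase 1) or a waiting list control and followed up for 6 months". It continues: "At the 6-month follow-up point, control participants will then be exposed to YES, in a phase 2 exposure". Both arms are then followed for another 6 months, and the longer phase 1 follow-up is meant to show whether the programme's effect lasts.

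Two other provisions bear on the between-arm contrast. Under Randomisation, "if young people decline randomisation they will be offered a preference for when they join the programme". Under Data collection and storage, "Analysis will be on-treatment, as the primary aim of this study is to assess feasibility".

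**The concern.** Any uncontrolled before/after comparison is open to a time trend. Weight in adolescents differs from most of the other listed outcomes because the direction of part of that trend is known beforehand: someone still growing gains weight whether or not the programme does anything. A rise after YES may then be growth, a programme effect or both. A real fall may be hidden.

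The consequence is limited but real. Unintended consequences of the programme are among the study objectives, and the curriculum has a session on food and weight, so a weight change after YES will invite interpretation. Choosing outcomes well for the definitive trial is also an objective, and an outcome that cannot be read in two of its planned contrasts is a weak candidate to carry forward. If height is not recorded when weight is taken, a later analysis plan cannot restore it for those visits.

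**Working it through.** The article gives no expected weight change, SD or growth rate, so there is no figure of its own to reproduce. The check takes each contrast in turn and then bounds the size under stated assumptions.

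**1. What each contrast estimates.** Let g be growth in kg per year, t the interval in years, and T the true programme effect on weight in kg.

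| Contrast | Expected value | Concurrent unexposed comparator? |
|---|---|---|
| Phase 1 arm, 0 to 6 months, before/after | 0.5g + T | Only if set against the control arm |
| Phase 1 minus control, change to 6 months, randomised | (0.5g + T) − 0.5g = T | Yes |
| Phase 1 arm, 0 to 12 months, before/after | g + T | No, controls are exposed from month 6 |
| Phase 2 arm, 6 to 12 months, before/after | 0.5g + T | No, all participants have been offered YES |

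Growth cancels in the second row only. The cancellation rests on randomisation, so it does not extend to participants who choose their phase, and an on-treatment analysis weakens it.

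**2. Size of the growth term (assumed g = 0 to 5 kg per year).** Growth contribution = g × t.
- Over 6 months: 0 × 0.5 = 0 kg to 5 × 0.5 = 2.5 kg.
- Over 12 months: 0 kg to 5 kg.

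**3. Share of a 6-month before/after change that is growth.** Share = 0.5g / (0.5g + T), with T also assumed.

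| g (kg/year) | T = 0.5 kg | T = 1 kg | T = 2 kg |
|---|---|---|---|
| 0.5 | 0.25/0.75 = 33% | 0.25/1.25 = 20% | 0.25/2.25 = 11% |
| 2 | 1/1.5 = 67% | 1/2 = 50% | 1/3 = 33% |
| 4 | 2/2.5 = 80% | 2/3 = 67% | 2/4 = 50% |

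If T = 0 and g > 0, the share is 100%. Growth is the larger part only when 0.5g exceeds T, and the documents cannot settle that.

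**4. How much the age mix matters.** The only age distribution in the article is the pilot's: mean 18, SD 1.7 years, 26 participants. If the trial's ages were normal with those values, the proportion under 16 would be Φ((16 − 18)/1.7) = 12%, and under 17 it would be Φ((17 − 18)/1.7) = 28%.

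As an illustration, assume yearly gain falls linearly from a at age 14 to b at age 19 and is flat after that.
- Ages uniform from 14 to 20: mean 12-month growth = (5/6)(a + b)/2 + (1/6)b. With a = 3 and b = 0.5 this is 1.46 + 0.08 = 1.54 kg. With a = 6 and b = 1 it is 2.92 + 0.17 = 3.08 kg.
- Pilot ages truncated to 14–20, same growth lines: 1.2 to 2.4 kg.

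An older mix shrinks the growth term but, under these assumptions, does not remove it.

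**5. Precision of the protected contrast.** With 25 per arm and 20% drop-out, 25 × 0.8 = 20 complete in each arm. The 95% half-width is 1.96 × SD × √(2/20). For an assumed SD of change of 2 kg it is ±1.2 kg, and for 5 kg it is ±3.1 kg. The contrast is unbiased by growth in expectation but imprecise.

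**The case against.** The strongest case against has four parts.

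- **Detail may sit elsewhere.** A condensed article gives weight one word. Whether it is analysed as kilograms, BMI or a standardised score, and whether height comes from records, may be settled in the full protocol or analysis plan. This stands in part. The missing derivation is not a finding, and the article never says that weight will be left unscaled. What the article does state is the measurement list and the before/after contrast, and scaling later depends on height having been recorded.
- **The same sentence plans the controlled comparison.** This stands. To 6 months the waiting-list controls grow too, and growth cancels in expectation for randomised participants. It does not help after month 6.
- **Lack of a late comparator affects every outcome.** True, but for weight in this age range the trend has a foreseeable direction, and a standard way to allow for it exists.
- **Weight carries little load.** This stands. The study is not powered for a clinical effect, and the progression criteria do not name weight.

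A reader might infer more: that weight change here mostly measures growth, that a gain after YES is guaranteed, or that the SD passed to the definitive trial would be materially inflated. The documents support none of these. In the tabulated cases the growth share runs from 11% to 80%, reaching 100% if YES has no effect, and the only age data point to an older group. A positive expected change need not appear as a clear observed gain. With an assumed SD of change of 4 kg and 20 completers, the standard error is 4/√20 = 0.89 kg, while the 6-month growth in the uniform-age illustration is 0.8–1.5 kg, or 0.9–1.7 standard errors. The SDs explicitly planned for the sample size are for HbA1c. Nor does any section plan to read weight gain as harm.

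**Conclusion.** The concern holds in a limited form. Read as written, the article commits body weight to before/after comparison in 14–19-year-olds and lists no height. For participants still growing, that comparison mixes growth with any programme effect. The phase 1 12-month change and the phase 2 6–12 month change cannot be corrected by a concurrent unexposed group. The 0–6 month between-arm contrast is sound in expectation for randomised participants, though imprecise.

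The size is unknown from the documents. The range of 0–2.5 kg over 6 months and 0–5 kg over 12 months rests wholly on an assumed growth rate of 0–5 kg per year, and an older sample such as the pilot's would tend towards the lower part of it. The severity is minor, and the change is worth making mainly because it is cheap and cannot be made after the visits have passed.

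**What to change.** - Add height to the data collected whenever weight is taken (baseline, 6 and 12 months).
- Define the outcome as change in age- and sex-standardised BMI (BMI SD score).
- If weight in kilograms is also shown, base any effect estimate on the 0–6 month contrast between randomised arms, adjusted for baseline weight, age and sex.
- Present before/after weight change in either arm as descriptive only, and say that it includes growth.

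The cost is one extra reading at each visit and a routine conversion. The downside is that the main result is no longer in kilograms and is less immediate for a lay reader. If the full protocol already records height, only the outcome definition and the reporting rule need to change.
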